### Data collection

After administering informed consent, RAs will complete the baseline survey with FP clients who agree to participate. The baseline survey will measure sociodemographic characteristics and key outcomes for difference-in-differences analysis. After completion of the baseline survey, the FP client will be walked back to the FP counseling waiting room (their previous place in line will be saved by clinic staff). When it is the participant’s turn, they will be seen for their appointment, during which the provider will deliver either the ARCHES intervention (at intervention health facilities) or standard FP counseling (at control health facilities). These services will be provided to all female FP clients at these health facilities regardless of whether they participate in the study. After the FP appointment, all participants will be directed back to the RA in a private room to complete a post-visit (exit) survey, be screened for distress, receive their compensation payment of 500 Kenyan shillings and written referrals, and schedule their six-month follow up visit. RAs will call participants to remind them of the scheduled six-month follow-up and reschedule as needed. On the day of the six-month follow-up visit, participants will return to the health facility or another location of their choosing to complete their follow-up survey. After completing their 6-month follow-up survey, participants will be given 1000 Kenyan shillings. A larger compensation payment will be given at follow-up to cover participant travel costs and to promote retention. All client surveys will be RA-administered and completed on tablets with the survey programmed in Open Data Kit (ODK), which will be programmed to require a response to all questions and other data quality controls such as including range checks for data values.

Providers trained as part of the study will complete a pre-training survey on the first day of training before any content is delivered, a post-training survey on the last day of training, and three-month and six-month follow-up surveys. Providers will not be compensated for their participation. Provider surveys will be self-administered on tablets with the survey pre-programmed in CommCare (Dimagi).

### Data management

Field supervisors will monitor RA data collection on a daily basis. Researchers at Population Council Kenya and UCSD will review electronic data for completeness and accuracy on a weekly basis. Researchers at UCSD will be responsible for variable coding for the primary analyses.

### Data analysis

Quantitative analyses to evaluate the effectiveness of ARCHES will use an intent-to-treat approach and assess the primary outcome using a multilevel mixed effects generalized linear regression model with logistic regression specifications for the binary outcome, accounting for facility-level clustering. For secondary outcomes, both single timepoint and difference-in-differences analyses will be used to compare treatment to controls, testing for an interaction between time and treatment. Difference-in-differences analyses will consider clustering within health facilities using nested random effects specifications due to repeated measurements over time of individuals nested within health facilities. Analyses will adjust for potentially relevant covariates measured at each time point. In addition to intent-to-treat analyses, we will conduct as-treated analyses to measure the effectiveness of the intervention among those who received ARCHES counseling compared to those who did not. We will also run exploratory analyses segregated by age group (age 15–24 and 25–49).

Survey items for the provider training evaluation will be tabulated and Pearson chi-square tests or T-tests (as appropriate for the outcome) at alpha < 0.05 will be used to compare responses to each item at pre-training and follow-up. For those with significant results, regression models accounting for health facility-level clustering will be used to assess the overall training effect on each outcome.

Missing client and provider data will be assessed for systematic differences between participants with missing and complete data. If systematic differences are observed, multiple imputation of missing data will be used to reduce bias.

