## Methods/design

### Design overview

We will use a mixed methods approach to evaluate ARCHES as adapted and implemented by the Kenya MOH in government health facilities in Uasin Gishu county, Kenya. We will conduct a cluster-randomized controlled trial (cRCT) with stratified randomization based on facility type and urban/rural location to evaluate the effectiveness of the adapted ARCHES intervention on unintended pregnancy 6-months post-intervention (see Additional File 1 for items from the WHO Trial Registration Data Set). This cRCT will include 24 randomly selected health facilities (total n = 3540 female clients seeking FP care at 24 facilities; facilities are randomly assigned to either intervention or control conditions, 12 facilities per condition) in Uasin Gishu county, Kenya. Data collection from clients (women and girls aged 15–49 seeking FP services from the 24 selected health facilities) will include a baseline survey (immediately prior to receiving care at the health facility), a post-visit or exit survey (at facility immediately after receiving care), and a 6-month follow up survey (Fig. 1). A sub sample of women and girls (n = 36) who received the intervention will also be invited for 3-month follow-up interviews to understand acceptability to clients. To evaluate provider training, we will conduct: 1) pre-training, post-training, 3-month, and 6-month follow-up post-training surveys from all ARCHES trained FP providers (n ~ 60), and semi-structured interviews 3-months post-training (n = 10) and one focus group discussion (FGD) 6-months post-training (n = 1, 6–8 participants) among these providers.

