#### Secondary outcomes

This study uses 15 secondary outcome measures, which can be found in Table 1 below. The IPV and RC outcomes assessments will include clients’ self-report of these forms of GBV at either baseline (at the facility prior to receiving care) or post-visit (at facility immediately after receiving care) and at six-month follow-up. We plan to use both reports at baseline and post-visit because, in the previous smaller ARCHES trial in Kenya, reporting of IPV and RC increased from baseline to post-visit among intervention clients despite no opportunity for new experiences of these forms of violence (i.e., clients had not left the clinic and partners were rarely present).

**Table 1 Tab1:** Secondary outcome measures

Secondary outcome measure	Definition	Timeframe
Modern contraceptive use in the past 6 months	Change in prevalence of self-reported modern contraceptive use in the past 6 months between baseline and 6-month follow-up in intervention compared to control group (difference-in differences)	Baseline (at facility prior to receiving care) and 6-month follow-up
Physical intimate partner violence in the past 6 months	Change in prevalence of self-reported physical intimate partner violence experience in the past 6 months between combined baseline/post-visit and 6-month follow-up in intervention compared to control group (difference-in differences)	
Sexual intimate partner violence in the past 6 months	Change in prevalence of self-reported sexual intimate partner violence experience in the past 6 months between combined baseline/post-visit and 6-month follow-up in intervention compared to control group (difference-in differences)	Baseline (combined report at facility prior to receiving care and report at facility immediately after receiving care (post-visit); combined due to increased reporting post-visit) and 6-month follow-up
Emotional intimate partner violence in the past 6 months	Change in prevalence of self-reported emotional intimate partner violence experience in the past 6 months between combined baseline/post-visit and 6-month follow-up in intervention compared to control group (difference-in differences)	Baseline (combined report at facility prior to receiving care and report at facility immediately after receiving care (post-visit); combined due to increased reporting post-visit) and 6-month follow-up

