### Power and sample size

In the previous ARCHES study conducted among private sector FP clients in Nairobi, incident unintended pregnancy at six months post-intervention, the primary outcome for the present study, was 1.72% among those receiving ARCHES and 3.13% among those receiving standard-of-care FP care (AOR 0.54) (unpublished). The present study is powered to detect an AOR of 0.54 in unintended pregnancy in the intervention group compared to the control group at an alpha of 0.15, assuming intra-class correlation of 0.1 from the previous trial (unpublished) and a six-month retention rate of 80% (6-month retention rate of 82% achieved in the previous trial, unpublished). Based on these assumptions, 1770 FP clients are needed at baseline enrollment per study arm (3540 clients total, average of 148 clients per facility with 50% cluster size variation) to detect a significant difference in incident unintended pregnancy at the six-month follow-up. We assumed a binomial outcome as it is unlikely women will experience more than one unintended pregnancy within the six-month follow-up window.

Although the commonly accepted threshold is alpha = 0.05, we chose a threshold of alpha = 0.15 as acceptable for a reduction in unintended pregnancy for the present study to balance the study cost (to power the study at alpha = 0.05, the required sample size would be approximately 22,000 clients) with the Kenya MOH’s priorities, which required a focus on unintended pregnancy as the primary outcome. The MOH views 85% certainty that an observed reduction in unintended pregnancy is a true effect as reaching practical significance for guiding health policy. This approach aligns with an ever-growing consensus among statisticians that p-values should be viewed as continuous, and always considered within the context of related prior evidence, plausibility of mechanism, and stakeholder perspectives regarding risk vs. benefits of action based on the implicated change [15]. Additionally, this sample size is sufficient to show significant change among secondary outcomes at alpha = 0.05 based on results from the prior trial.

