### Allocation

A total of 24 government health facilities in Uasin Gishu county were randomly selected for study participation. This cluster-randomized controlled trial used parallel assignment to two arms: (1) the intervention arm will implement the ARCHES intervention integrated in the BCS + counseling strategy, and (2) the control arm will implement standard contraceptive care using the BCS + approach. Researchers at UCSD compiled a list of the 24 facilities and stratified based on facility type (hospital, health center, or dispensary) and urban or rural location, and used SAS to generate random numbers to randomize an equal number of facilities to the intervention and control groups within these strata. All FP clients enrolled in facilities assigned to the intervention group are considered intervention group participants, and all FP clients enrolled in facilities assigned to the control group are considered control group participants.

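### The nested random effects named for the difference-in-differences models do not provide for facilities changing differently over time, so ten secondary-outcome tests can exceed their nominal 5%

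*Protocol article*

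**What the plan says.** The Data analysis section compares arms on change over time by "testing for an interaction between time and treatment". It says that these analyses take account of facility clustering "using nested random effects specifications due to repeated measurements over time of individuals nested within health facilities". The section names no facility-by-time effect and does not exclude one.

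The Secondary outcomes section states: "This study uses 15 secondary outcome measures". By count of Table 1, ten are defined as difference-in-differences and five as single-time-point comparisons. The ten are:

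- **Binary (seven):** modern contraceptive use; physical, sexual and emotional intimate partner violence; reproductive coercion; covert contraceptive use; awareness of violence services.
- **Scores (three):** contraceptive self-efficacy; self-efficacy to use violence services; attitudes to reproductive coercion.

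The Power and sample size section sets the level for these outcomes when it says that "this sample size is sufficient to show significant change among secondary outcomes at alpha = 0.05". Under Allocation, the researchers "used SAS to generate random numbers to randomize an equal number of facilities to the intervention and control groups", so the facility is the unit of randomisation, with "12 facilities per condition".

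**The concern.** In a trial that randomises facilities, the error term for a comparison of changes must include how much facilities differ in their changes. A facility intercept captures only how much facilities differ in level. If the fitted model has just facility and person intercepts, two facilities that drift apart for reasons unrelated to the intervention contribute about 118 women each, as though those women had changed independently.

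The design gives reasons to expect some such drift. Care at the facility falls between the baseline and the follow-up measurements. About 60 ARCHES-trained providers serve the 12 intervention facilities, roughly five each, so many women share a provider. Training and mentorship act through facility staff in both arms. Surveys are interviewer-administered, and the Secondary outcomes section reports that disclosure of violence and coercion rose between baseline and post-visit in the previous trial without new exposure.

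The affected outcomes include violence, coercion and contraceptive use. The Dissemination section says that the results will inform scaling to other counties and countries. Intervals that are too narrow could present chance differences between facility trends as intervention effects.

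**Working it through.** **Inputs from the article**

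- 24 facilities, 12 per arm.
- Cluster size: "average of 148 clients per facility with 50% cluster size variation"; 3540 / 24 = 147.5.
- Retention: "a six-month retention rate of 80" per cent, so m = 147.5 x 0.8 = 118 women per facility at six months.
- CV of cluster size 0.5, so 1 + CV² = 1.25.
- Level 0.05, taken as two-sided because the article does not say.

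**Inputs not in the article (assumed)**

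- Intraclass correlation (ICC) of the secondary outcomes: 0.01 to 0.10.
- Share of facility variance that is stable over time (S): 0.80 to 1.
- Within-woman correlation over time, for the continuous case: 0.5.

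**Step 1: what cancels.** Write an outcome as facility effect + facility-by-time effect + person effect + residual. In a woman's change between two time points, the facility and person effects drop out. What remains is the difference of two facility-by-time effects (variance s_ct² each) and of two residuals (variance s_e² each). With complete data, a linear model with only facility and person intercepts therefore gives the same interaction test as an unclustered comparison of individual changes. This was confirmed by fitting such a model to six simulated data sets with 20 women per facility. The mean interaction standard error was 0.0957, the unclustered standard error was 0.0957, and the standard error from facility means averaged 0.124.

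**Step 2: how far the variance is understated (continuous outcome, total variance 1)**

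- s_ct² = ICC x (1 - S)
- s_e² = (1 - ICC) x (1 - 0.5)
- Ratio true/model = [s_e² + m(1 + CV²) s_ct²] / (s_e² + s_ct²), with m(1 + CV²) = 118 x 1.25 = 147.5
- Type I error = 2[1 - Φ(1.96 / √ratio)]

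Example, ICC 0.05 and S = 0.80: s_ct² = 0.05 x 0.20 = 0.010; s_e² = 0.95 x 0.5 = 0.475; ratio = (0.475 + 1.475) / 0.485 = 4.02; type I error 32.8%. A within-woman correlation of 0.4, with the small s_ct² dropped from the denominator, gives 1 + 1.475 / 0.57 = 3.59, so the result does not hinge on that choice.

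**Step 3: null simulation.** 24 facilities, mean 118 women, CV 0.5. There were 4000 runs per continuous scenario and 2000 per binary scenario. The binary check used a conditional-logit (discordant-pair) test, with the ICC on the latent scale.

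| ICC | S | Continuous, formula | Continuous, simulated | Binary, simulated |
|---|---|---|---|---|
| 0.10 | 1.00 | 5.0% | 4.8% | 5.9% |
| 0.01 | 0.95 | 6.7% | 6.8% | not run |
| 0.01 | 0.90 | 8.5% | 8.1% | 6.3% |
| 0.01 | 0.80 | 12.0% | 11.5% | not run |
| 0.02 | 0.90 | 12.1% | 12.4% | 7.2% |
| 0.02 | 0.80 | 18.5% | 18.3% | 10.9% |
| 0.05 | 0.90 | 21.7% | 22.0% | 11.9% |
| 0.05 | 0.80 | 32.8% | 31.5% | 18.1% |
| 0.10 | 0.95 | 22.5% | 22.1% | not run |
| 0.10 | 0.90 | 33.8% | 33.2% | 18.6% |
| 0.10 | 0.80 | 46.6% | 44.7% | 26.8% |

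The first row reproduces the plan's nominal 5% when no facility changes differently from the others.

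**Step 4: the alternative.** A t-test on facility mean changes gave 4.6% to 5.4% in every scenario, continuous and binary.

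**The case against.** **The defect is inferred.** The specification is one summary sentence in a journal article. It does not list the model terms, and the full random-effects structure may sit in an analysis plan that is not shown. A reader might infer that the plan excludes a facility-by-time effect, or ignores clustering for these outcomes. The text does not support that. It does, however, name a structure and justify it by repeated measurements on individuals. That structure, read naturally, is valid only in the special case of no differential facility change.

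**The inflation is not known.** A reader might infer that the false-positive rates are well above 5% as a matter of fact. They depend on a variance that the article does not give, and they run from no inflation upward. It is also tempting to use the ICC of 0.1 as the plan's own value, which gives the largest figures. That value was stated for the primary outcome's sample size, and carrying it over to the secondary outcomes is an assumption.

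**Most of the outcomes are binary.** Seven of the ten are, and the simulated inflation is smaller there: 26.8% against 44.7% at ICC 0.10 with 80% stable. The two ICC scales are not identical, but the continuous figures should not be quoted for all ten.

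**One range will not fit every outcome.** Four of the ten also use a post-visit measurement on the day of baseline, to which six-month drift does not apply. Facility-level change is also less obviously a driver of partner violence than of contraceptive use. Both points stand.

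**The primary outcome is untouched.** It is a single-time-point comparison with a model stated to account for facility clustering. The five single-time-point secondary outcomes are likewise outside this point.

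**Conclusion.** The concern holds in conditional form. Facility and person intercepts alone do not carry facility-level change into the error term of the time-by-treatment test, although facilities were randomised. The ten tests can then exceed 5%.

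With 118 women followed per facility and CV 0.5, simulated type I error is about 7% to 45% for continuous outcomes (ICC 0.01 to 0.10, 80 to 95% of facility variance stable). For binary outcomes it is about 6% to 27% (latent-scale ICC 0.01 to 0.10, 80 to 90% stable). These ranges rest on assumed ICCs, stability and within-woman correlation, and on a two-time-point comparison with complete data. The cancellation is exact for the linear model; for binary outcomes it rests on the conditional-logit simulation.

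The correction is worth making before analysis. It ranks below must-fix because only secondary outcomes are involved and the true facility-by-time variance is unknown.

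**What to change.** In the difference-in-differences models, add a facility-by-time random effect (a facility random slope on time) alongside the facility and person intercepts. Test the interaction on facility-level degrees of freedom: 24 - 2 = 22, less those used for the strata. Three facility types by two locations make at most six strata, hence at most five further degrees of freedom. Alternatively, compare facility mean changes between arms, which held 4.6% to 5.4% in all scenarios above. If the analysis plan already contains such a term, saying so in one sentence settles the point.

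The cost is one sentence and one model term, with no new data. Confidence intervals will be wider wherever facilities do change differently, so the statement that the sample size suffices for the secondary outcomes should be rechecked against that wider error.

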### Aims

Our primary aim is to increase voluntary use of modern FP methods and ultimately decrease unintended pregnancy among female FP clients in Uasin Gishu county, Kenya by addressing barriers to successful FP uptake and use including RC, IPV, and inferior quality of healthcare (QOC) via adaptation and implementation of ARCHES.

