### Outcome measures

#### Primary outcome

The primary outcome is incident unintended pregnancy in the past 6 months, which is a binary variable coded to 1 if the woman reports unintended pregnancy and 0 otherwise. The study will assess the difference in self-reported unintended pregnancy in the past 6 months at the 6-month follow-up in the intervention compared to control group (single time point analysis).

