Use of intimate partner violence services	Difference in prevalence of use of intimate partner violence services in the past 6 months at the 6-month follow-up in intervention compared to control group (single time point analysis)	6-month follow-up
Attitudes accepting of reproductive coercion	Change in mean attitude score (range: 6–12, higher = attitudes less accepting of reproductive coercion/improved attitudes) between baseline, post-visit, and 6-month follow-up in intervention compared to control group (difference-in differences)	Baseline (at facility prior to receiving care), Post-visit (at facility immediately after receiving care), and 6-month follow-up
Quality of family planning care	Difference in mean interpersonal quality of family planning scale (range: 11–55, higher = higher quality) at post-visit in intervention compared to control group (single time point analysis)	Post-visit (at facility immediately after receiving care)
Discontinuation of modern contraception	Difference in prevalence of modern contraceptive discontinuation in the past 6 months at the 6-month follow-up in intervention compared to control group (single time point analysis)	6-month follow-up

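### The covariate rule does not limit adjustment to pre-intervention variables, so the intent-to-treat models can include variables that ARCHES itself changes

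*Protocol article*

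**What the plan says.** In the Protocol article, Data analysis says that the effectiveness analyses "will use an intent-to-treat approach and assess the primary outcome using a multilevel mixed effects generalized linear regression model", with a logistic specification and allowance for facility clustering. It goes on to single-timepoint and difference-in-differences analyses of the secondary outcomes, and then gives the covariate rule: "Analyses will adjust for potentially relevant covariates measured at each time point". The next sentence introduces as-treated analyses as an addition to the intent-to-treat ones, so the rule belongs to the intent-to-treat analyses.

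Design overview lists the client surveys as a baseline survey before care, "a post-visit or exit survey (at facility immediately after receiving care), and a 6-month follow up survey". Data collection says of the first of these: "The baseline survey will measure sociodemographic characteristics and key outcomes for difference-in-differences analysis". The primary comparison is of "self-reported unintended pregnancy in the past 6 months at the 6-month follow-up in the intervention compared to control group (single time point analysis").

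Aims describes how the trial expects to raise FP use and lower unintended pregnancy: "by addressing barriers to successful FP uptake and use including RC, IPV, and inferior quality of healthcare (QOC"). Table 1 measures several links of that chain after the visit or at 6 months, for example: "Difference in prevalence of modern contraceptive discontinuation in the past 6 months at the 6-month follow-up in intervention compared to control group".

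No covariate is named, and nothing excludes variables that the intervention may change.

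**The concern.** Randomising facilities identifies the total effect of being assigned to ARCHES. Adjusting for baseline variables leaves that target in place. Adjusting for a variable that the intervention has altered does not. If the variable lies on the path to unintended pregnancy, the part of the effect that runs through it is removed. If it also shares an unmeasured cause with the outcome, conditioning on it can create an association between arm and outcome where there is none.

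The primary odds ratio is what the Kenya MOH intends to use for policy, judged at an alpha of 0.15. An estimate that left out the effect acting through contraceptive use or reduced RC would answer a different question from the one in Aims, while carrying the intent-to-treat label.

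**Working it through.** **1. Which variables the rule admits.** There are three client time points, and two of them (post-visit and 6 months) come after counselling. The only survey for which the article mentions sociodemographics is the baseline survey. The post-visit and 6-month measures that it names are those in Table 1: method uptake, use, covert use and discontinuation, RC, IPV, self-efficacy, awareness and use of services, attitudes, and quality of care.

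**2. Whether they can respond to arm.** The article gives three reasons to think so.
- Aims names FP uptake and use, RC, IPV and quality of care as the route of action.
- Background reports that in the earlier Nairobi trial ARCHES lowered the odds of leaving without a modern method, which is a post-visit variable.
- Secondary outcomes reports that in the earlier trial disclosure of IPV and RC rose between baseline and post-visit among intervention clients, with no chance of new events. Post-visit RC and IPV can therefore differ by arm through reporting alone.

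**3. Reproducing the stated effect.** Power and sample size says that 6-month unintended pregnancy "was 1.72% among those receiving ARCHES and 3.13% among those receiving standard-of-care FP care (AOR 0.54) (unpublished"). From the two rates:

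OR = (0.0172/0.9828) / (0.0313/0.9687) = 0.01750/0.03231 = 0.542, which agrees with 0.54.

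**4. Effect of adjusting for a mediator.** The documents give no mediator figures, so these are assumptions. Let the covariate be non-use of modern contraception at 6 months, with prevalence q0 in controls and q1 under ARCHES, and let risk in non-users be R times that in users.
- Control risk in users: r = 0.0313 / [(1 − q0) + R·q0]
- Remaining direct risk multiplier: k = 0.0172 / {r·[(1 − q1) + R·q1]}

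Example with q0 = 0.30, R = 10, q1 = 0.15: r = 0.0313/3.70 = 0.00846, and k = 0.0172/(0.00846 × 2.35) = 0.865. A logistic model on the exact expected cell counts gives OR 0.542 without the covariate and 0.857 with it.

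| q0 | R | Adjusted OR, no reduction in non-use | 25% reduction | 50% reduction |
|---|---|---|---|---|
| 0.30 | 5 | 0.536 | 0.624 | 0.747 |
| 0.30 | 10 | 0.531 | 0.657 | 0.857 |
| 0.20 | 15 | 0.523 | 0.651 | 0.859 |

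The unadjusted OR is 0.542 in all nine cells. In the no-reduction column the small shift reflects the fact that an odds ratio changes when a prognostic covariate is added. It is not loss of the intervention effect.

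**5. Effect of conditioning when there is no true effect.** Assumptions: an unmeasured factor present in 30% of clients raises outcome risk 3- or 6-fold; the covariate has prevalence 15% without the factor and 45% with it; ARCHES multiplies that prevalence by 0.5 or 0.8; arm has no effect on pregnancy. The true OR is 1.00. The adjusted OR is 1.02 to 1.09.

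Both illustrations ignore facility clustering. They show how the estimate moves and do not reproduce the planned mixed model.

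**The case against.** The fair case on the other side has four parts.

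- **No covariate is named.** RC, IPV, uptake and quality of care appear in Table 1 as outcomes, and nowhere as adjustment variables. Data collection separates sociodemographics from key outcomes, so a reader may take covariates to mean demographics. This stands: the text permits mediators but does not announce them. It does not remove the problem, because nothing excludes them and no post-baseline demographics are mentioned to give the words about each time point a harmless meaning.
- **The sentence follows the description of repeated-measures models,** where time-varying covariates are ordinary language. This is plausible, but the sentence speaks of analyses without qualification and the text around it is about intent-to-treat. The primary model is not excluded. Adjusting a difference-in-differences model for a post-visit mediator would raise the same difficulty.
- **A covariate list is normally left to the SAP.** Agreed, and a missing list is not the point. The point is a rule that the article does state. An SAP that followed it faithfully would carry it forward.
- **The size is assumed.** Agreed. It is shown only as a range.

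**Conclusion.** The rule is badly fixed and should be corrected. As written it lets variables affected by the intervention into the intent-to-treat models, including the primary one, and the estimate could then depart from the total effect of assignment.

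The documents do not determine by how much. Under the mediator assumptions above (non-use 20–30% in controls, risk 5–15 times higher in non-users), a total OR of 0.54 is estimated at 0.52–0.54 if the covariate is unaffected by arm, 0.62–0.66 if ARCHES cuts non-use by a quarter, and 0.75–0.86 if it halves it. For a mediator of a protective effect the expected direction is towards 1, but neither direction nor size follows from the text alone.

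Stronger readings are tempting and are not supported:

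- *That mediators will be adjusted for and the primary odds ratio will be biased.* The covariates are unnamed, and if those chosen do not respond to arm the shift is negligible.
- *That a single figure describes the bias.* Assuming that half the log odds ratio is mediated gives exp(0.5 × ln 0.54) = 0.73, but the half is arbitrary and the result is one scenario among many.
- *That covariates will be picked after follow-up data are seen.* The article does not say when they are chosen.
- *That the rule leads to overfitting.* At the planning rates and 80% retention, 1770 × 0.8 = 1416 per arm gives about 44 + 24, or some 69 events. That limits any long covariate list, baseline-only ones included, so it is not a consequence of this sentence.

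**What to change.** Replace the covariate sentence in Data analysis with:

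*Intent-to-treat models for the primary and secondary outcomes adjust only for prespecified covariates measured in the pre-visit baseline survey and for the randomisation strata (facility type, urban/rural location).*

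Place any analysis that uses post-visit or 6-month covariates in a separately labelled exploratory or mediation analysis.

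One consequence should be made explicit. The combined baseline/post-visit report of RC and IPV contains post-visit information. Its use in defining the RC and IPV outcomes is not touched by this change, but under the new sentence only the pre-visit report could serve as a covariate.

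The cost is one sentence and no new survey, since the pre-visit survey is already part of the design. The downside is that any gain in precision from time-varying covariates is given up.
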